| Secondary  | To assess the safety, tolerability and reactogenicity profile of the candidate vaccine ChAdOx1 nCoV-19  | a) occurrence of solicited local reactogenicity signs and symptoms for 7 days following vaccination;
b) occurrence of solicited systemic reactogenicity signs and symptoms for 7 days following vaccination;
c) occurrence of unsolicited adverse events (AEs) for 28 days following vaccination ;
d) change from baseline for safety laboratory measures and (except groups 4, 6, 9 and 10);
e) Occurrence of disease enhancement episodes | a) Day 0-7 Self-reported symptoms recorded using electronic diaries
b) Day 0-7 Self-reported symptoms recorded using electronic diaries
c) Day 0-28 Self-reported symptoms recorded using electronic diaries
d) See schedule of attendances
e) Throughout the study |

CONFIDENTIAL

|  |                                                                                                                               |                                                                                                                                                                                                                                                                                                                                                                              |                                                                                            |
|--|-------------------------------------------------------------------------------------------------------------------------------|------------------------------------------------------------------------------------------------------------------------------------------------------------------------------------------------------------------------------------------------------------------------------------------------------------------------------------------------------------------------------|--------------------------------------------------------------------------------------------|

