|          | schedules for groups 1, 2, 7 and 8 only) | 
 
b) occurrence of solicited systemic reactogenicity signs and symptoms for 7 days following booster vaccination;
 
c) occurrence of unsolicited adverse events (AEs) for 28 days following booster vaccination;
 
d) change from pre-booster for safety laboratory measures and;
 
e) Occurrence of disease enhancement episodes
 
f) Antibodies against SARS-CoV-2 spike protein at Day 56 post-vaccination.
 
g) Proportion of seroconversion to antibodies against SARS-CoV-2 spike protein from baseline at Day 56 post-vaccination.
 
 | 
 
b) Day 28-35 Self-reported symptoms recorded using electronic diaries
 
c) Day 28-56 Self-reported symptoms recorded using electronic diaries
 
d) See schedule of attendances
 
e) Throughout the study
 
f) Blood samples drawn at day 0, 28 and at day 56.
 
g) Blood samples drawn at day 0, 28 and at day 56.
 
 |
| Tertiary | Exploratory Immunology                   | 
 
a) virus neutralising antibody (NAb) assays against live and/or pseudotype SARS-CoV-2 virus
 
b) Cell analysis by flow cytometry assays
 
c) Functional antibody assays
 
d) Anti-vector immunity induced by 1 or 2 doses of ChAdOx1 nCoV-19
 
                                                                                                                                                                                                                                                                                                          | See schedule of attendances                                                                                                                                                                                                                                                                                                                                                                             |

CONFIDENTIAL

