## CONFIDENTIAL

an extra 5mL of blood should be added to the overall cumulative blood volume. aSubject to site capacity, sample and test availability. b Optional Stool sample at approximately 7 days after onset of symptoms for those who have a positive SARS-CoV-2 NAAT test result and possibly again at 14 days after symptom onset if necessary. c Participants enrolled in group 5b will only have B-cell immunology assessments whereas those in group 5c will have both B and T-cell immunology assessments.

CONFIDENTIAL

**Table 10** Schedule of attendances for participants in group 4c, 1a3, 1a4, 2a3, 2a4, 5a3, 5a4 and 6b (booster) *Protocol V19: Unblinding /* provision of treatment procedures will occur concurrently (Table 14) to these procedures.

| Attendance Number (boost)                                     | 1
V2
(booster)       | 2                | 3                   | 4                    | 5                    | COVID-19
Testing | COVID-19
NAAT
positive + 7
days | COVID-19
Follow-up | Extra Visit                                                                      |
|---------------------------------------------------------------|----------------------------|------------------|---------------------|----------------------|----------------------|---------------------|------------------------------------------|-----------------------|----------------------------------------------------------------------------------|
| Timeline**
(days)                                          | > 4 weeks
post
prime | 28 post
boost | 90
post
boost | 182
post
boost | 364
post
boost | As required         | 7 days post
NAAT
positive          |                       | At time of
early
unblinding
before
receipt of
deployed
vaccine |
| Time window (days)                                            | +14                        | ±7               | ±14                 | ±14                  | ±30                  | N/A                 | -2, +7                                   |                       | N/A                                                                              |

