| Attendance Number (boost)                              | 1
V2
(booster) | 2           | 3           | 4           | 5                  | COVID-19
Testing   | COVID-19
NAAT
positive + 7
days | COVID-19
Follow-up | Extra Visit |
|--------------------------------------------------------|----------------------|-------------|-------------|-------------|--------------------|-----------------------|------------------------------------------|-----------------------|-------------|
| Weekly household exposure
questionnaire             |                      | ongoing     |             |             |                    |                       |                                          |                       |             |
| Medical History                                        | (X)                  | (X)         | (X)         | (X)         | (X)                | (X)                   | (X)                                      |                       |             |
| Physical Examination (if necessary)                    | (X)                  | (X)         | (X)         | (X)         | (X)                | (X)                   | (X)                                      |                       |             |
| Biochemistry, Haematology (mL)                         |                      |             |             |             |                    |                       |                                          |                       |             |
| Exploratory immunology (mL)                            | up to 50             | up to
50 | up to
50 | up to
50 | up to
50        | up to 50 d |                                          |                       | (up to 50)  |
| PAXgenes                                               |                      |             |             |             | (2.5) p | 2.5                   |                                          |                       |             |
| Nose/Throat Swab and/or saliva
sample               |                      |             |             |             |                    | X                     |                                          |                       |             |
| Stool sample a,b                            |                      |             |             |             |                    |                       | (X)                                      | (X)                   |             |

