| Weekly PCR sample a                         |                      | ongoing     |             |             |                    |                       |                                          |                       |             |
| Urinary bHCG (women of
childbearing potential only) | X                    |             |             |             |                    |                       |                                          |                       |             |
| Blood volume per visit                                 | 50                   | 50          | 50          | 50          | 50                 | up to 52.5            |                                          |                       | up to 50    |
| Cumulative blood volume %                   | 50                   | 100         | 150         | 200         | 250                | 302.5                 | 302.5                                    |                       | 352.5       |

S = screening visit; (X) = if considered necessary; \*\* Timeline is approximate only. Exact timings of visits relate to the day on enrolment, ie, each visit must occur at indicated number of days after enrolment  $\pm$  time window. Where a second dose is administered, the window will apply to the time their last vaccination took place. ^Only temperature will be routinely measured at subsequent follow-up visits. At COVID-19 testing visits a full set observations will be taken, including respiratory rate and oxygen saturation. % Cumulative blood volume for volunteers if blood taken as per schedule,

CONFIDENTIAL

and excluding any repeat safety blood test that may be necessary. Blood volumes may vary according to local site equipment and practices. a Subject to site capacity, sample and test availability. d Optional and subject to site capacity. s A subset of up to 1000 volunteers will be asked to fill an e-diary with reactogenicity symptoms for 7 days only in groups 4, 6, 9 and 10. p Pax genes sample at D364 to be done only on participants that have attended at least one COVID-19 testing visits within the trial, an extra 2.5mL should be added to the cumulative blood volume when this applies. b Optional Stool sample at approximately 7 days after onset of symptoms for those who have a positive SARS-CoV-2 NAAT test result and possibly again at 14 days after symptom onset if necessary.

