S = screening visit; (X) = if considered necessary; \*\* Timeline is approximate only. Exact timings of visits relate to the day on enrolment, ie, each visit must occur at indicated number of days after enrolment  $\pm$  time window. Where a second dose is administered, the window will apply to the time their last vaccination took place. ^Only temperature will be routinely measured at subsequent follow-up visits. At COVID-19 testing visits a full set observations will be taken, including respiratory rate and oxygen saturation. % Cumulative blood volume for volunteers if blood taken as per schedule, and excluding any repeat safety blood test that may be necessary. Blood volumes may vary according to local site equipment and practices. a Subject to site capacity, sample and test availability. d Optional and subject to site capacity. s A subset of up to 1000 volunteers will be asked to fill an e-diary with reactogenicity symptoms for 7 days only in groups 4, 6, 9 and 10. p Pax genes sample at D364 to be done only on participants that have attended at least one COVID-19 testing visits within the trial, an extra 2.5mL should be added to the cumulative blood volume when this applies. b Optional Stool sample at approximately 7 days after onset of symptoms for those who have a positive SARS-CoV-2 NAAT test result and possibly again at 14 days after symptom onset if necessary. \*\*\* For participants who previously declined to have a second dose of vaccine but now wish to complete study vaccine following unblinding

CONFIDENTIAL

Table 12 Schedule of attendances for participants in group 11.

| Attendance Number                                                | 1 | 2
V1 | 3  | 4 V2 | 5                                | 6                                 | 7                                     | 8                                     | COVID-
19
Testing | COVID-19
NAAT
positive +7
days
(Remote) | COVID-
19
Follow-
up |
|------------------------------------------------------------------|---|---------|----|------|----------------------------------|-----------------------------------|---------------------------------------|---------------------------------------|-------------------------|-----------------------------------------------------|-------------------------------|

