#### **9.14 Safety Group Holding Rules**

These safety holding rules apply to ChAdOx1 nCoV-19 vaccine only. Solicited, unsolicited and laboratories adverse events will be systematically collected in groups 1, 2, 5, 7 and 8. A sub-set of up to 1000 participants in each of Groups 4, 6, 9 and 10 will be asked to record solicited and unsolicited AEs for 7 days only.

- **Solicited local adverse events:**
  - If more than 25% of doses of the vaccine at a given time point (e.g. Day 0, Day 28) in a study group are followed by the same Grade 3 solicited local adverse event beginning within 2 days after vaccination (day of vaccination and one subsequent day) and persisting at Grade 3 for >72 hrs
- **Solicited systemic adverse events:**
  - If more than 25% of doses of the vaccine at a given time point (e.g. Day 0, Day 28) in a study group are followed by the same Grade 3 solicited systemic adverse event beginning within 2 days after vaccination (day of vaccination and one subsequent day) and persisting at Grade 3 for >72 hrs

- **Unsolicited adverse events:**
  - If more than 25% of doses of the vaccine at a given time point (e.g. Day 0, Day 28) in a study group are followed by the same Grade 3 unsolicited adverse event beginning within 2 days after vaccination (day of vaccination and one subsequent day) and persisting at Grade 3 for >72 hrs
- **Laboratory adverse event:**
  - If more than 25% of doses of the vaccine at a given time point (e.g. Day 0, Day 28) in a study group are followed by the same Grade 3 laboratory adverse event beginning within 3 days after vaccination and persisting at Grade 3 for >72 hrs
- **A serious adverse event considered possibly, probably or definitely related to vaccination occurs**
  - If an SAE occurs in any one individual, which is possibly, probably or definitely related to vaccination this would trigger a holding rule. There are two exemptions from this rule, which would not activate a holding rule. These include:
    - COVID-19 related hospital admissions considered to be at least possibly related to ChAdOx1 nCoV-19 (e.g. if considered to be a clinical presentation of a disease enhancement episode). COVID-19 related SAEs will be regularly reviewed by the DSMB, and a single event will not trigger a holding rule.
    - SAEs reported under the Hy's Law requirement will not necessarily trigger a holding rule. These cases will also be reviewed by the DSMB

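### Table 10 schedules no safety bloods at or after the booster for groups 1a3, 1a4, 2a3 and 2a4, although a secondary endpoint requires change from pre-booster laboratory values in older two-dose groups

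*Protocol*

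**What the plan says.** Section 4 of the protocol has a secondary objective on the safety and immunogenicity of a booster in adults aged 56 or older, restricted to the two-dose schedules of groups 1, 2, 7 and 8. Its laboratory outcome reads "d) change from pre-booster for safety laboratory measures and", with timing referred to the schedule of attendances. The Synopsis carries the same outcome and adds change from baseline.

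A separate, general secondary safety outcome is "change from baseline for safety laboratory measures and (except groups 4, 6, 9 and 10"; those four groups are the only exceptions.

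Section 9.14 states: "Solicited, unsolicited and laboratories adverse events will be systematically collected in groups 1, 2, 5, 7 and 8".

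The Synopsis and section 5.1 describe 1a3, 1a4, 2a3, 2a4, 5a3 and 5a4 as two-dose groups, filled by invitation from 1a, 2a and 5a. Their booster schedule in section 7.3.3 is Table 10: "Schedule of attendances for participants in group 4c, 1a3, 1a4, 2a3, 2a4, 5a3, 5a4 and 6b (booster". In that table the row "Biochemistry, Haematology (mL" is empty at the booster visit, at days 28, 90, 182 and 364 post boost, at the COVID-19 visits and at the extra visit. Table 5, for groups 1b, 2b, 5d, 7b and 8b, schedules 5 mL of safety blood at the boost and at 3, 7 and 28 days after it. "Table 12 Schedule of attendances for participants in group 11" also has a blank laboratory row.

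**The concern.** An endpoint that takes its timing from a schedule with no sample cannot be computed for the groups on that schedule. If laboratory safety after the booster is then summarised over the older two-dose groups, the Table 10 participants enter either as missing or, worse, as people without laboratory events, when nobody looked.

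The gap does not fall evenly. It removes one prime-boost regimen entirely from the scheduled laboratory follow-up of older adults, so a statement about booster laboratory safety at age 56 and over would rest on other regimens. Section 5.4 describes transient cytopenias after other adenoviral-vectored vaccines, while judging them not clinically significant, and section 9.4 lists thrombocytopenia among the events to be monitored.

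**Working it through.** **1. Is the blank row real, or lost in reading the PDF?** The line "Cumulative blood volume" settles this, because it must equal the sum of the scheduled draws.

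- Table 10 states 50, 100, 150, 200, 250, then 302.5 (testing visit) and 352.5 mL (extra visit). With immunology blood only: 5 × 50 = 250; 250 + 50 + 2.5 (PAXgene) = 302.5; 302.5 + 50 = 352.5. All are reproduced with 0 mL of safety blood.
- If 5 mL were drawn at the booster visit and at day 28 post boost, the line would read 55, 110, 160, 210, 260, then 312.5. It does not.
- As a control, Table 5 moves from 182.5 to 237.5 at the boost (50 + 5), to 242.5 at 3 days (5), to 297.5 at 7 days (50 + 5), and from 347.5 to 402.5 at 28 days (50 + 5). It closes only with the safety bloods included.
- Table 12: 6 × 50 = 300; 300 + 52.5 = 352.5; 352.5 + 52.5 = 405, as stated, again with 0 mL of safety blood.

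The blank rows are therefore what the protocol schedules.

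**2. Does another table fill the gap?** Table 4 (1a, 2a) and Table 9 (5a) schedule safety bloods at screening, at day 0 if needed, and at days 3, 7 and 28 after the prime, with nothing later. The day 28 sample could stand in for a pre-booster value if the boost followed soon after. Neither table gives a post-boost value. Section 7.2 allows further safety bloods where clinically relevant, at the investigator's discretion, which does not yield systematic endpoint data.

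**3. How many participants?** Planned numbers from the Synopsis and section 5.1:

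| Older two-dose groups | ChAdOx1 nCoV-19 | MenACWY | Total |
|---|---|---|---|
| 1b, 2b, 7b, 8b (post-boost bloods scheduled) | 30 + 50 + 30 + 50 = 160 | 10 + 10 + 10 + 10 = 40 | 200 |
| 1a3/1a4, 2a3/2a4 (none scheduled) | up to 30 + 50 = 80 | up to 10 + 10 = 20 | up to 100 |
| All | up to 240 | up to 60 | up to 300 |

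Share unmeasured: 100/300 = 33%; among ChAdOx1 nCoV-19 recipients, 80/240 = 33%.

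**4. Which regimen?** Among older adults only groups 1 and 2 have the Abs 260 prime. Groups 1b and 2b are boosted with 2.2 × 10^10 vp (qPCR). The Abs 260 prime with the 0.5 mL PS80-corrected boost is therefore planned only in 1a3 and 2a3, which are exactly the 80 without scheduled bloods.

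**5. Groups 5 and 11.** The pre-booster endpoint does not include them. For 5a3/5a4 (up to 50 + 50 = 100) the conflict is with section 9.14 and, after the boost only, with the general change-from-baseline endpoint; Table 9 supplies post-prime values. For group 11 (up to 60) it is only that the group is missing from the exceptions to the general endpoint while Table 12 has no safety bloods.

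**The case against.** The strongest reply is that the booster objective was written for the randomised 4-6-week arms. Its other timings (days 28-35, days 28-56, bloods at days 0, 28 and 56) fit Table 5, where the boost is at day 28. They do not fit participants first randomised to one dose and later invited to a boost at the earliest opportunity. Appendix A shows that those boosts were added at version 11.0, so the objective may simply not have been updated. This is a plausible explanation of how the mismatch arose, but it does not remove it: the current text names the two-dose schedules of groups 1 and 2 without exempting 1a3, 1a4, 2a3 or 2a4, and section 9.14 names the whole groups.

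Three stronger readings might be inferred, and the documents do not support them.

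- That the endpoint is lost altogether. It remains measurable in 1b, 2b, 7b and 8b.
- That the laboratory safety rules fail in these groups. The individual rule in section 9.14.1 governs further vaccination. Post-prime bloods are scheduled and the booster is the last planned dose, so no later decision is lost. The group holding rule looks for onset within 3 days of a dose, and Table 10 has no visit before day 28 post boost, so the rule could not be assessed after these boosts. That mattered only until section 9.14 declared the group rules no longer applicable after emergency-use approval.
- That the 0.5 mL PS80-corrected product has no post-boost laboratory data at all. Groups 5d and 12 (ages 18-55) have scheduled post-boost bloods, and 8b participants boosted with it do too.

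**Conclusion.** The contradiction stands. Table 10 cannot deliver an endpoint that section 4 assigns to the groups it governs, nor the systematic collection that section 9.14 claims. Up to 100 of 300 planned older two-dose participants are affected, and one regimen in older adults has no scheduled post-boost laboratory value.

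The 33% is a ceiling: the numbers for 1a3, 1a4, 2a3 and 2a4 are maxima that depend on acceptance of the invitation, while the other 200 are taken at their planned size. The count leaves out boosts at Extra Visit B, which also carries no scheduled safety bloods. Discretionary samples may exist for some people but would be selected on clinical grounds.

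This limits what can be concluded about booster laboratory safety in older adults. It does not bear on efficacy, on the reactogenicity or serious adverse event outcomes, or on laboratory follow-up after the prime.

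**What to change.** Reconcile Tables 10 and 12 with sections 4 and 9.14, by one of two routes.

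- Where boosts are still to be given, add the 5 mL biochemistry and haematology sample to two draws that Table 10 already schedules: the booster visit, before the dose, and 28 days post boost. This restores the endpoint but not the group holding rule, which needs values within days of the dose. The cost is one extra tube at each of two existing venepunctures, plus laboratory work.
- Otherwise, restrict the change-from-pre-booster endpoint to 1b, 2b, 7b and 8b, correct the section 9.14 sentence so that it does not claim post-boost laboratory collection in the Table 10 groups, and add group 11 to the exceptions to the general laboratory endpoint. The cost is wording and a narrower safety claim. Since section 7.6.1 already provides for unblinding of all participants, this is probably the route for most of them.

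Under the second route, and for any boost already given without samples, report post-boost laboratory safety in these groups as not measured, with denominators counting only participants sampled, and never as an absence of laboratory adverse events.
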